## 240 **2) Comparative Period – Control Group**

241 (Standard care [oral care, Episil® oral liquid, etc.] only)

- 242 • Record the start date of the comparative period.
- 243 • Participants receive only standard care as per routine practice (see Section 6 for concomitant
- 244 treatments).
- 245 • After the comparative period evaluation, during the continuous period (Day 1–14/21/28), the
- 246 investigational device will be applied using the same procedure as the intervention group.
- 247 • Device removal, dislodgment recording, and discontinuation criteria are handled identically
- 248 to the intervention group.

## 249 **(5) Management of the Investigational Device**

250 The procedures for managing the investigational device used in this study are as follows:

### 251 **1. Device Delivery**

- 252 ○ The Coordinating Investigator will request Sun Medical Co., Ltd. to deliver the
- 253 investigational device.
- 254 ○ Before the first delivery, each Site Investigator will prepare a *Device Management*
- 255 *Log* to record the receipt and usage of the device at their site.

256                   ○ Upon delivery, the designated Device Manager will verify the quantity and condition  
257                   of the received devices, record the necessary details in the log, and thereafter manage  
258                   the inventory.

259       **2. Storage and Handling**

260                   ○ Each Site Investigator will store and handle the device in accordance with the storage  
261                   conditions specified in Section 4(4) of this protocol.

262       **3. Device Distribution**

263                   ○ Based on usage requests, the Device Manager will distribute the required number of  
264                   devices and document the relevant information in the management log.

265       **4. Handling of Used Devices**

266                   ○ Each Site Investigator will record the date of use, quantity used, quantity returned,  
267                   and subject identification code for used devices, and ensure proper disposal.

268       **5. Post-Study Device Management**

269                   ○ After study completion, each Site Investigator will verify that the quantities of  
270                   unused and used devices match the records in the management log.

271                   ○ Any discrepancies will be investigated, and the reason will be documented in the log.

272                   ○ Once reconciliation is complete, remaining devices will be disposed of appropriately,  
273                   and all disposal records will be archived together with the management log.

274

275       **(6) Concomitant Medications and Therapies**

276       **1. Permitted Medications / Therapies**

277                   • Standard oral care focusing on moisturization, mucosal protectants (e.g., *Episil*® oral liquid),  
278                   and mouth rinses.

279                   • Chemotherapy for the primary disease (including oral or intravenous steroids, continuous  
280                   anti-inflammatory analgesics, and G-CSF administration during hematologic suppression).

281                   • Treatments for comorbidities or intercurrent illnesses during the study period.

282                   • As-needed use of anti-inflammatory analgesics is permitted for symptom relief.

283                   ○ The preferred agents are loxoprofen sodium 60 mg tablets or acetaminophen 200–  
284                   300 mg tablets, standardized per institution.

285                   ○ The same analgesic should be used consistently during the study period.

286                   ○ The name, dosage, and number of tablets taken as needed will be recorded in the  
287                   patient diary.

- Analgesics for fever or cancer-related pain may be co-administered.

## **2. Prohibited Medications / Therapies**

- Oral steroid ointments (except as rescue medication; the number of uses must be recorded).
- Narcotics or opioid analgesics.
- Non-urgent dental treatments.
- Radiotherapy to the head and neck region.

If any concomitant medication or therapy is used, its content and timing must be recorded.

**Rationale:** The allowance of concomitant anti-inflammatory analgesics aims to minimize patient discomfort and avoid undue burden.

## **(7) Case Registration and Randomization**

### **1. Informed Consent, Preliminary Registration, and Assignment of Subject Code**

The Site Investigator (or sub-investigator) will conduct a preliminary eligibility check under routine clinical care.

After providing a full explanation of the study, written informed consent will be obtained. The participant will then be preliminarily registered in the EDC system, and a subject identification code will be assigned.

### **2. Screening Examination Prior to Full Registration**

After consent, the investigator will conduct screening tests according to the study schedule (see p.7).

Based on the results, eligibility will be confirmed—participants who meet all inclusion criteria and none of the exclusion criteria will be deemed eligible and fully registered in the EDC system.

### **3. Full Registration and Randomization**

Following full registration in the EDC system, randomization information will be generated automatically through the same system, assigning each participant to either the intervention or control group.

### **4. Method of Randomization**

Before the start of the study, the Randomization Supervisor will prepare a reproducible randomization table using computer-generated random numbers.

A stratified block randomization method will be applied, stratified by study site planned to conduct the comparative period.

The allocation ratio between the intervention and control groups will be **1:1**, based on the planned total sample size.

As this is an open-label study, detailed algorithmic parameters of the randomization will not be described in this protocol to prevent predictability of assignment and potential selection bias. Instead, they are specified in a separate *Randomization Specification Document*, which will remain confidential until all participants have been assigned.

## **(8) Post-Study Care**

After completion of this study, the Site Investigator (or sub-investigator) will provide medical care deemed most appropriate for each participant, incorporating any findings or outcomes obtained from the study.

## **(9) Use of Specimens and Data from Other Institutions**

Because this confirmatory study is a multicenter collaborative trial, patient data from the following participating institutions will be utilized:

- Shikoku Cancer Center
- Miyagi Cancer Center
- Sagara Hospital

# **5. Observations and Assessment Items**

## **(1) Participant Background**

- Age at consent, medical history\*, comorbidities\*\*, primary disease classification (breast cancer), drug/food allergies, smoking history, alcohol consumption, and body weight.
- Presence and site of oral mucositis lesions (upper/lower labial vestibule, dorsal/right/left/ventral/tip of tongue, buccal mucosa).
- Planned date of starting the comparative period (Day 1) and details of concurrent chemotherapy regimen (agents, cycle presence, cycle duration).
- History of prior radiotherapy (excluding head and neck region) and timing.
- Presence of oral candidiasis.

\* **Medical history:** diseases clinically significant between 1 year prior to registration and enrollment, and other resolved conditions ( $\geq 1$  year before registration) judged relevant to participant background.

\*\* **Comorbidities:** diseases with ongoing symptoms at the time of registration.

## **(2) Evaluation and Examination Items**

### **Screening Period**

- Confirmation of participant background.
- Interview and physical examination (for study purposes).
- Hematology (RBC, hemoglobin, hematocrit, WBC, neutrophils, platelets) – performed within routine clinical care.
- Blood biochemistry (total protein, albumin, AST, ALT, Na, K, Cl, BUN, creatinine, CRP) – within routine clinical care.
- Pain and QOL scores:
  - Oral mucositis grading by CTCAE v5.0 (MedDRA/J v25.1) and CTCAE v3.0,
  - PRO-CTCAE #3a and #3b,
  - EORTC QLQ-OH15 #35,
  - Numerical Rating Scale (NRS) for pain at affected sites.
- Presence, site, and onset of oral mucositis.
- Oral findings (number of remaining teeth, presence of dentures, periodontal examination performed or not, untreated teeth).
- Intraoral photographs.
- Panoramic radiograph.
- Confirmation of concomitant drugs/therapies.
- ECOG Performance Status (PS).
- G-CSF administration (yes/no).

### **Comparative Period**

- Interview and physical examination.
- Hematology (as above).
- Blood biochemistry (as above).
- Pain and QOL scores (CTCAE v5.0 / v3.0, PRO-CTCAE #3a, 3b, EORTC QLQ-OH15 #35, pain NRS).
- Presence, site, and timing of oral mucositis.
- Presence and timing of oral candidiasis.
- Intraoral photographs.
- Confirmation of concomitant medications/therapies.

- Evaluation of procedural factors.
- Patient preference or acceptability of the investigational treatment.
- ECOG PS.
- Patient diary entries (once daily) including:
  - Device dislodgement (presence/absence),
  - Pain intensity (PRO-CTCAE #3a, #3b; EORTC QLQ-OH15 #35; pain NRS),
  - Number of as-needed anti-inflammatory analgesic tablets,
  - Number of uses of oral steroid ointment as rescue medication,
  - Use of *Episil*® oral liquid (yes/no).
- Adverse events.
- Device malfunctions.
- G-CSF administration (yes/no).

#### **Continuous Period**

Assessments identical to those conducted in the comparative period.

#### **(3) Interview on General and Local Conditions**

General and local physical conditions will be confirmed through interviews, and ECOG PS will be evaluated at each visit.

#### **(4) Confirmation of Adverse Events, Illnesses, and Device Malfunctions**

All adverse events, illnesses, and device malfunctions will be recorded in the electronic Case Report Form (eCRF), including details, onset/resolution dates, severity, treatment, outcome, seriousness assessment, and causal relationship to device use.

Follow-up investigations will be performed as needed.

Events occurring prior to device removal due to chemotherapy delay will also be included in safety evaluations.

Symptoms or disease progression attributable to the primary malignancy or to anticancer therapy itself will not be considered adverse events in this study.

For participants allocated to the control group during the comparative period, assessment of device-related malfunctions or causality is not applicable.

413 Schedule

| Period                                     | Screening period
a) / Enrollment     | Comparative period                   |                                              |                                    | Continuous period:
When chemotherapy is administered after the comparative period, existing therapy is combined with the filling of the investigational device irrespective of group assignment. |
|--------------------------------------------|-----------------------------------------|--------------------------------------|----------------------------------------------|------------------------------------|-----------------------------------------------------------------------------------------------------------------------------------------------------------------------------------------------------|
| Assessment date                            | —                                       | Day of study procedure
(Day 1) g) | End of comparative period (Day 14 / 21 / 28) | (At discontinuation)               | End of continuous period (Day 14 / 21 / 28)                                                                                                                                                         |
| Allowable range                            | Day -56 to Day -1
(before procedure) | Assessment date (Day 0)              | Assessment window: Day -7 to +7              | Discontinuation date (Day 0 to +1) | Assessment window: Day -7 to +7                                                                                                                                                                     |
| re-screening for eligibility               | ○                                       |                                      |                                              |                                    |                                                                                                                                                                                                     |
| Obtaining informed consent                 | —                                       |                                      |                                              |                                    |                                                                                                                                                                                                     |
| Pre-registration and eligibility screening | ●                                       |                                      |                                              |                                    |                                                                                                                                                                                                     |
| Verification of subject background         | ●                                       |                                      |                                              |                                    |                                                                                                                                                                                                     |
| Final registration and randomization       | ●                                       |                                      |                                              |                                    |                                                                                                                                                                                                     |
| Interview / Physical examination / ECOG PS | ●                                       | ● c)                      | ●                                            | ●                                  | ●                                                                                                                                                                                                   |
| Administration of G-CSF (yes/no)           | ●                                       | ●                                    | ●                                            | ●                                  | ●                                                                                                                                                                                                   |
| Blood tests (hematology and biochemistry)  | ● i)                         |                                      | ●                                            | ●                                  | ●                                                                                                                                                                                                   |

- c) Assessments marked accordingly must be performed prior to the investigational procedure.
- d) If the investigational device dislodges before the end of any treatment period, the date and time of dislodgement must be recorded in the patient diary.
- e) For participants assigned to the control group during the comparative period, the specified assessments and examinations for the comparative period are not required.
- f) Symptoms or disease progression related to the underlying breast cancer, as well as events directly caused by chemotherapy, are not regarded as adverse events in this study. Events occurring before device removal due to chemotherapy delay will still be evaluated. For participants in the control group during the comparative period, assessment of causal relationship between adverse events and device filling is not applicable.
- g) The day on which participants visit the site for device application prior to chemotherapy shall be defined as Day 1 (start of the comparative period). Chemotherapy should be administered within 0–3 days after device application, and the actual chemotherapy date must be recorded. If chemotherapy is postponed, the device should be temporarily removed, and the device application date reset in accordance with the rescheduled chemotherapy.
- h) Evaluate whether natural dislodgement, brushing-related dislodgement, meal-related dislodgement, or self-removal by the participant occurred. If such events occur before temporary device removal due to chemotherapy delay, they must also be included in the evaluation.
- i) If hematology or biochemistry tests performed for routine clinical purposes within 56 days prior to obtaining consent are available, they may be used as the screening examination data.

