## **4. Study Methods**

### **(1) Study Type and Design**

This is a multicenter, prospective, open-label, randomized, parallel-group comparative study.

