#### **1. Full Analysis Set (FAS):**

All participants who were randomized, received treatment, and had at least one efficacy assessment (primary or secondary).

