### **(4) Protocol Amendments**

Safety-related information will be continuously reviewed, and the protocol and consent documents will be amended if necessary.

All amendments must be approved in advance by the Certified Review Board (CRB).

Amendments will be submitted to MHLW as follows:

739       • **Substantial amendment:**

- 740           1. *Notification of change in implementation plan* (Form No. 2, Ministerial Ordinance)  
741           2. *Revised implementation plan*

742       • **Minor amendment:**

- 743           1. *Notification of minor change in implementation plan* (Form No. 3)  
744           2. *Revised implementation plan*

745 For minor administrative changes (e.g., investigator contact details, institutional name updates),  
746 notification to the CRB will be made within 10 days, accompanied by submission of Form No. 3 to  
747 MHLW.  
748

749 **(5) Criteria for Discontinuation**

750 When continuation is deemed impossible, the investigator shall discontinue the participant's  
751 involvement, explain the reason if appropriate, and ensure that post-discontinuation medical care is  
752 provided without disadvantage.

753 **Reasons for discontinuation include:**

- 754       1. Participant requests to withdraw. (The reason will be confirmed if possible, but not required.)  
755       2. Worsening of primary disease, chemotherapy-related symptoms, or requirement for  
756       disallowed concomitant therapy.  
757       3. Occurrence of adverse events making continuation difficult.  
758       4. Noncompliance with the protocol.  
759       5. Ineligibility determined upon further observation after registration.  
760       6. Any other reason judged by the investigator to make continuation inappropriate.

761 **In case of treatment discontinuation:**

762 If continuation of the investigational treatment is deemed impossible for the above reasons, treatment  
763 will be discontinued with an appropriate explanation to the participant.

764 Participants who have received the investigational device will continue safety follow-up observations  
765 even after discontinuation.  
766

767 **15. Storage and Disposal of Study Records and Data (Including Retention Period)**

768 The principal investigator shall prepare and maintain records regarding:

- 769       1. Identification of each study participant.

2. Clinical care and testing performed for participants.
3. Details related to study participation.

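### Open-label allocation may be released at any time from Day -56 to Day -1 with no stated limit to Day 1, so participants can leave the analysis set, and the target site and baseline are fixed, with the arm known

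*Protocol*

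**What the plan says.** **Timing of randomisation.** In the Section 5 Schedule, the row "Final registration and randomization" has one mark, in the screening and enrolment column. The allowable range of that column is "Day -56 to Day -1 (before procedure". This agrees with Section 4(3), which gives a screening period of 1–56 days.

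**Sequence.** Under Section 4(7), consent and preliminary registration come first, then screening tests. After these, "participants who meet all inclusion criteria and none of the exclusion criteria will be deemed eligible and fully registered in the EDC system". Following full registration, "randomization information will be generated automatically through the same system". Section 4(1) describes the trial as a "multicenter, prospective, open-label, randomized, parallel-group comparative study". No maximum interval from allocation to Day 1 is given.

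**Day 1.** The visible schedule repeats the interview, examination and ECOG status on Day 1 but marks no eligibility confirmation there. A row "re-screening for eligibility" is marked in the screening column; its conditions, and schedule notes a) and b), cannot be read in the text available for this review.

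**After registration.** Section 14(5), item 5, lists as a reason for discontinuation: "Ineligibility determined upon further observation after registration".

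**Analysis set.** Section 8(1) defines the FAS as "All participants who were randomized, received treatment, and had at least one efficacy assessment (primary or secondary".

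**Target site and baseline.** The Note on Evaluations in Section 6 requires the target site to be identified on Day 1 in both arms. Section 8(2) cross-tabulates the Day 1 grade against later grades and defines success by the change at that site.

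**The concern.** Each rule is ordinary by itself. Together they open a route out of the primary analysis while the arm is known. Several entry conditions in Section 10 can change over weeks: absence of candidiasis, ECOG 0–1, chemotherapy still scheduled, opioid or oral steroid ointment use, possible pregnancy, planned dental work. The revision table gives chemotherapy delay from poor patient condition as a reason for the wider window, so changes of status before Day 1 are foreseen.

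A participant who withdraws or is judged ineligible in that interval does so, or is so judged, with the allocation known. The FAS then requires treatment. This may act unequally: an intervention participant needs a device placed, whereas control treatment is routine standard care, and the protocol does not say when that counts as begun.

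The same timing affects the endpoint. Which tooth–mucosa contact counts as the target, and its grade on Day 1, decide whether a participant can succeed by staying free of mucositis or by improving. Both are recorded after the arm is known. At stake are the comparability of the arms and, to a smaller degree, power.

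**Working it through.** **1. The plan's own figure.** Inputs from Section 7: success 50% and 25%, two-sided 5%, power 90%, Pearson chi-square, 1:1.

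n = [1.960·√(2·0.375·0.625) + 1.2816·√(0.5·0.5 + 0.25·0.75)]² / 0.25²
= (1.3419 + 0.8477)² / 0.0625 = 76.7, so 77 per group.

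This reproduces the stated 77 exactly; power at 77 is 90.1%. The target equals the calculated number, so it holds no allowance for loss.

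**2. Number who could leave the FAS.** The protocol gives no rate; 5–15% is an assumption.

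- 0.05 × 154 = 7.7, about 8
- 0.15 × 154 = 23.1, about 23

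**3. Power under equal loss in both arms (assumed rates).** Excluded: n = 77(1−d) per arm, with 50% against 25%. Counted as failures: n = 77 per arm, with both success rates multiplied by (1−d).

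| Loss d | n per arm if excluded | Power, excluded | Power, counted as failures |
|---|---|---|---|
| 5% | 73.2 | 88.6% | 87.6% |
| 10% | 69.3 | 86.8% | 84.7% |
| 15% | 65.5 | 84.8% | 81.4% |
| 20% | 61.6 | 82.6% | 77.8% |

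The last column matters for the remedy. Keeping lost participants in the analysis as failures protects the comparison but costs more power than dropping them, so preventing the loss is better than handling it afterwards.

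**4. Worst-case bias.** Assume no true effect, 35% success in both arms (an assumed rate, not from the protocol), and k would-be failures leaving one arm only.

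Spurious difference = 0.35·77/(77−k) − 0.35

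- k = 4: 26.95/73 − 0.35 = 1.9 points
- k = 8: 26.95/69 − 0.35 = 4.1 points
- k = 12: 26.95/65 − 0.35 = 6.5 points

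This is an upper illustration. It supposes that everyone who leaves would have failed and that the other arm loses nobody. The planned difference is 25 points.

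**The case against.** The strongest reply is that the 56 days cover the whole of consent, screening and enrolment. Randomisation comes last in that sequence and may fall on Day -1; sites may in practice randomise shortly before the procedure. The re-screening row may already deal with changed eligibility, and its conditions cannot be read here. Before chemotherapy nobody can know who will fail, so strongly selective loss is unlikely. Control participants who continue chemotherapy receive the device in the continuous period (Sections 4(3) and 4(4)), which gives them a reason to stay. The power cost of moderate equal loss is small.

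Much of this stands, and it rules out several stronger readings:

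- A reader might infer that participants will be lost. The protocol shows a route and gives no rate.
- A reader might infer that allocation occurs eight weeks ahead. That is only the outer limit.
- A reader might add the postponement rule in schedule note g) to the gap. That note concerns removing a device already placed and resetting its date, so those intervention participants have been treated.
- A reader might take item 5 of Section 14(5) as the only applicable rule. Items 2 and 6 can apply too. Item 5 is also not confined to the time before Day 1: someone found ineligible after treatment can remain in the FAS if assessed.

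What the reply does not remove: nothing visible limits the interval, the re-screening row sits in the same pre-Day 1 column and is not shown to precede allocation, and even allocation on Day -1 precedes the choice of target site and the baseline grade.

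**Conclusion.** The point holds as a design risk, not as a prediction of loss. The protocol allows open-label allocation anywhere in the window once screening is complete, states no limit to Day 1, and defines the FAS so that untreated randomised participants fall out. It also fixes the target site and baseline after the arm is known, and this follows from the schedule whatever the loss.

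Under the assumed ranges the power cost is modest: 88.6–82.6% against 90.1% for equal loss of 5–20% per arm. The difference of about 2 to 6.5 points is a one-arm worst case at an assumed success rate and should not be read as the expected bias. The statement that no eligibility check is marked on Day 1 rests on the visible schedule and should be checked against notes a) and b) and the re-screening row in the full table. The matter is worth correcting because the remedy is cheap, not because the damage is shown to be large.

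**What to change.** 1. Keep Day -56 to Day -1 for consent, preliminary registration and screening.
2. Move final registration and randomisation to Day 1, before the procedure. The order would be: complete the baseline assessments, record the target site or sites, re-confirm all inclusion and exclusion criteria in the EDC, then release the allocation. A participant who fails the re-check is a screen failure and is never randomised.
3. Where same-day allocation is not feasible, state a short maximum interval between allocation and Day 1. This limits the loss but leaves the target site and baseline exposed.
4. Define the primary analysis set to include everyone randomised, and keep them in follow-up whether or not study treatment is given or continued. The one exception is a participant whom data recorded before randomisation show never to have met the criteria. This concerns follow-up and analysis only, not when treatment should stop.

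**Cost.** One schedule row moves and the EDC gains one form step; allocation is already generated automatically, and Day 1 assessments are already due in both arms. The real burden is that the dentist must be available at every Day 1 visit without knowing the arm in advance.

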**(3) Planned Participation Period per Subject**

**29 to 112 days**

- **Screening Period:** 1–56 days
- **Comparative Period:** 14, 21, or 28 days
  - The standard duration will be 21 days regardless of allocation.
  - If chemotherapy is administered in treatment cycles, the period will correspond to one cycle.
  - Minor adjustments due to outpatient schedules are permissible.
- **Continuous Period:** 14, 21, or 28 days
  - After completing the comparative period, participants continuing chemotherapy will receive both standard care (oral care, Episil® oral liquid, etc.) and the investigational device, irrespective of group assignment.

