## ② Intervention Procedures

The comparative period (Day 1) begins on the day the investigational device is applied prior to chemotherapy. Chemotherapy should be initiated within three days after device placement (Day 0–3).

The evaluation timepoints are scheduled for Day 14, 21, or 28 of each treatment period, depending on the chemotherapy regimen.

After baseline assessments and interviews on Day 1 (before chemotherapy), interventions are conducted as follows:

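### The ±7-day window for the primary mucositis reading is not capped at the next chemotherapy cycle, so the latest allowed reading falls 3 to 6 days after that cycle's first dose

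*Protocol*

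**What the plan says.** Section 4(3) of the protocol sets the length of the comparative period: "The standard duration will be 21 days regardless of allocation", and "If chemotherapy is administered in treatment cycles, the period will correspond to one cycle". It adds that small shifts to suit clinic appointments are acceptable.

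Section 4(4)② fixes the clock: "The comparative period (Day 1) begins on the day the investigational device is applied prior to chemotherapy". It continues: "The evaluation timepoints are scheduled for Day 14, 21, or 28 of each treatment period". Note g to the Schedule in section 5 adds: "Chemotherapy should be administered within 0–3 days after device application, and the actual chemotherapy date must be recorded".

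The allowable-range row of the same Schedule gives the end-of-comparative-period visit an "Assessment window: Day -7 to +7". The CTCAE v3.0 grade taken in that period is the primary endpoint (section 6(1)).

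For controls, section 4(4)② 2) introduces device filling with "After the comparative period evaluation, during the continuous period (Day 1–14/21/28), the" and says the procedure is that of the intervention group. The Schedule's column header assigns chemotherapy given after the comparative period to the continuous period, together with filling in both arms.

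**The concern.** The design counts in whole cycles, but the visit window does not respect the cycle boundary. One cycle with small appointment shifts is one rule. A week either side, with no limit at the next dose, is another.

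The primary outcome compares two readings at the target site: no mucositis at both, or a lower grade at the second (section 8(2), Definitions). It therefore depends on when the second reading is taken. A reading after the next cycle has begun reflects two cycles of chemotherapy, while the endpoint is meant to describe one.

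There is also a conflict over sequence. A control patient read that late would already have entered the next cycle, although filling is placed after the evaluation and the Schedule couples that cycle with filling. The passages must be reconciled.

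**Working it through.** **The plan's own duration figure.** Section 4(3) gives 29 to 112 days of participation. Adding the shortest and longest nominal periods (screening, comparative, continuous) reproduces it:

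- shortest: 1 + 14 + 14 = 29
- longest: 56 + 28 + 28 = 112

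The figure rests on nominal lengths. With the window applied to both visits the extremes would be 1 + 7 + 7 = 15 and 56 + 35 + 35 = 126.

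**Inputs for the overrun.**

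- Cycle length and nominal reading day C = 14, 21 or 28 (sections 4(3) and 4(4)②).
- Day 1 is device placement (section 4(4)②).
- Lag from placement to chemotherapy, 0 to 3 days (note g), so the first dose is on Day 1 + lag.
- Window −7 to +7 days (Schedule).
- Assumption: the next cycle starts on time, on Day 1 + lag + C. Where a cycle has several doses, this means the first dose of the next cycle.

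**Formulas.**

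- Overrun = last allowed day − next-dose day = (C + 7) − (1 + lag + C) = 6 − lag. C cancels, so the result is the same for all three cycle lengths.
- Days from first dose to reading: earliest (C − 7) − (1 + lag), latest (C + 7) − (1 + lag).

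**Results.**

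| C | Allowed days | Next dose (lag 0 to lag 3) | Latest reading after next dose (lag 0 to lag 3) | Days from first dose to reading, over all lags |
|---|---|---|---|---|
| 14 | Day 7–21 | Day 15–18 | 6, 5, 4, 3 days | 3–20 |
| 21 | Day 14–28 | Day 22–25 | 6, 5, 4, 3 days | 10–27 |
| 28 | Day 21–35 | Day 29–32 | 6, 5, 4, 3 days | 17–34 |

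**Share of the window.** It holds 7 + 1 + 7 = 15 days. With lag 0 the next dose is on Day C + 1, so Days C + 2 to C + 7, which is 6 of the 15, lie strictly after it. The dose day itself is not counted, because a reading can still precede the dose that day. For a 14-day cycle the 15-day window is longer than the cycle.

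**What causes the overrun.** If days were counted from chemotherapy as Day 1 with the same +7, the overrun would be (C + 7) − (1 + C) = 6 days for every patient. Counting from placement gives 6 − lag, which is never more. The uncapped +7 side is therefore the cause. The placement anchor only adds up to 3 days of variation in time since chemotherapy.

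**If the next cycle is late.** A delay of x days reduces the overrun to 6 − lag − x, so a delay of 6 days or more removes it altogether.

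**The case against.** The strongest reply is that the protocol already implies the right order. The period is one cycle, filling follows the evaluation, filling is done before chemotherapy, and later chemotherapy belongs to the continuous period. A site following this would read the patient before the next dose. That is probably the intention. It is not written as a rule in the visible text, and the explicit window permits otherwise, so the reply supports a clarification and does not remove the need for one.

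A second reply is that the Schedule as read here is incomplete: it shows no row for CTCAE grading, and its notes begin at c). If the full table caps the reading at the next dose, the point falls away.

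A third is that the figures are maxima. They need a next cycle on time and the late end of the window. Participants with no further chemotherapy cannot overrun. The shortest interval, 3 days after chemotherapy, needs a 14-day regimen, chemotherapy on Day 4 and the earliest allowed visit all at once, whereas the standard period is 21 days. All of this stands.

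A reader might also infer that open-label investigators could pick the date to suit an arm. The documents do not show this. The window is the same in both arms, date shifts are tied to clinic appointments, and this exposure is common to open-label grading and would remain under any window.

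**Conclusion.** The point holds as a gap between the one-cycle definition and the visit window. With the next cycle on time, the latest allowed reading falls 3 to 6 days after its first dose, and with chemotherapy on Day 1, 6 of the 15 allowed days lie strictly after the next-dose day. It is worth correcting because it touches the primary endpoint and costs almost nothing.

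Two stronger readings are tempting and not supported. One is that counting from device placement causes the overrun; the arithmetic shows that a lag after placement shortens it. The other is that the trial no longer measures one cycle, or that its primary comparison is biased. Only readings taken after the next dose leave the one-cycle definition. The documents give neither the share of such readings nor a time course for mucositis, so neither bias nor loss of power can be computed. The 77 per group in section 7 does not depend on the window and is unaffected.

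**What to change.** State in the Schedule and in note g that, for participants continuing chemotherapy, the end-of-comparative-period CTCAE v3.0 reading is taken within the existing window and before the first dose of the next cycle. The window then closes at the actual next dose and stays usable if that dose is delayed. Reconcile this wording with sections 4(3) and 4(4)② 2), so that evaluation, filling and next chemotherapy are described in one consistent order.

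Keep any reading taken after that dose in the primary analysis, flag it as a deviation, and add a sensitivity analysis without such readings. Excluding them outright would lose primary outcomes from a 154-patient trial.

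Counting the visit day from the recorded chemotherapy date is an optional refinement. It removes up to 3 days of timing variation but does not cure the overrun on its own.

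The cost is slightly less scheduling flexibility and a few flagged readings. No visit should be added, since participants who continue chemotherapy already attend for device placement beforehand.
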